### Outcome Measures

#### Overview

The outcomes are assessed at baseline, postintervention, and 30-day posttransplant follow-up. All measures are performed by trained study personnel at the Dana-Farber Cancer Institute. Postintervention assessment (week 10; visit 27) includes a reassessment of baseline measures. The 30-day post-ASCT follow-up (week 14-15; visit 28) consists of a reassessment of baseline measures (not including dual-energy x-ray absorptiometry [DEXA]) in addition to Hematopoietic Cell Transplantation-Comorbidity Index, length of hospital stay, readmission rates, and treatment-related adverse events. If the intervention is selected following the ASCT recovery period, the waitlist control group testing (visits 29-54) includes assessment of baseline measures (not including DEXA) pre- and postintervention (visits 29 and 54, respectively).

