### Sample Size

We anticipate recruiting 1-2 participants per month, based on the accrual rates (3 to 4 participants per month) of previous exercise intervention studies [48]. A total of 30 eligible participants will be entered into this study and randomly assigned to the intervention and the control groups in a 1:1 ratio (15 per group). The sample size is based on general recommendations (24 to 50) for pilot studies in general [49-51] and this study provides 80% power to detect the effect size of Cohen *d*=1.15 (taking account of 10% dropout) at .05 two-sided α level.

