### Statistical Analysis

The primary analysis is a mean difference in percent change from baseline (week 0, preintervention), between the intervention and the control groups in lower leg muscle strength over 2 time points: pretransplant (week 9, postintervention), and posttransplant (week 14-15, 30-day post-ASCT follow-up). Linear mixed-effects models are used to compare the between-group differences at postintervention and follow-up after adjusting for baseline value of the outcome and covariates, where the intervention indicator and time are included as fixed effects and participants are included as random effects. From previous studies, the estimated standard deviation of change in muscle strength (measured through leg press) from baseline to pretransplant is 16.8 kg. Thus, this study will detect a between-group mean difference of 19.3 kg with 80% power. The primary analyses will be based on the intention-to-treat principle including all randomized participants. The same analyses will also be performed with the per-protocol population.

To test hypotheses related to differences in physical capacity, patient-reported outcomes, and cardiometabolic health outcomes across groups at study completion, standard statistical techniques are used to assess within-group differences among each end point (ie, 2-tailed *t* test or Wilcoxon signed rank test, proportions, and corresponding 95% exact CI, etc) and between-group differences (ie, 2-tailed *t* tests, two-sample Wilcoxon tests, generalized linear mixed-effects model for longitudinal measurements, and so on). As an exploratory analysis to assess group differences, each clinical outcome as continuous variables (ie, length of hospital stay and the number of comorbidities) and categorical variables (ie, hospital readmission) is analyzed using 2-sample *t* tests for continuous variables and Fisher exact test will be used for analyzing categorical variables. An exploratory analysis to assess differences in the postintervention self-elected exercise for the waitlist control group will be assessed for end points of aim 1-2 using paired *t* tests and Cohen d is calculated to determine the effect size.

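### Secondary outcomes: within-group tests are listed for hypotheses about group differences, and no baseline adjustment is named although baseline values are collected

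*Protocol article*

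**What the plan says.** All references are to the protocol article.

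- **Statistical Analysis, first paragraph.** The primary outcome, lower limb strength, is analysed with a linear mixed-effects model that adjusts for the baseline value and covariates.
- **Statistical Analysis, second paragraph.** The hypotheses for the secondary outcomes concern differences across groups. To test them, "standard statistical techniques are used to assess within-group differences among each end point"; the examples are a t test or signed rank test, and proportions with exact intervals. The same sentence adds between-group methods: t tests, two-sample Wilcoxon tests and a generalized linear mixed-effects model for longitudinal data. Both lists are left open. No baseline term is named and no method is identified as the decisive one.
- **Statistical Analysis, clinical outcomes.** These are labelled exploratory. The plan takes "each clinical outcome as continuous variables (ie, length of hospital stay and the number of comorbidities" and compares them by two-sample t test.
- **Outcome Measures, Overview.** Baseline measures are repeated after the intervention and at the 30-day post-transplant visit, except DEXA, which is omitted at the latter. The 30-day visit repeats them "in addition to Hematopoietic Cell Transplantation-Comorbidity Index, length of hospital stay, readmission rates, and treatment-related adverse events". The comorbidity index is listed at no other visit.
- **Tertiary Outcomes.** The clinical outcomes, including the comorbidity index, come from medical record review.

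**The concern.** There are two problems in how the secondary analysis is set out.

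First, the hypothesis and part of the method do not match. A paired or signed rank test asks whether one arm changed from its own baseline. In a small trial, one arm can cross p<.05 and the other miss it when the arms have changed by the same amount. If such a result is read as a group difference, the error rate is no longer 5%.

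Second, the trial collects baseline values for these outcomes and uses them in its primary model, but the secondary plan does not carry that adjustment over. With about 13 patients per arm, chance imbalance at baseline feeds directly into an unadjusted comparison of follow-up values, and precision is lost.

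The primary analysis is not affected, but most of the outcomes the trial will report are.

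**Working it through.** **Inputs.** From Sample Size: "randomly assigned to the intervention and the control groups in a 1:1 ratio (15 per group"); dropout and alpha from "1.15 (taking account of 10% dropout) at .05 two-sided α level"; power from "this study provides 80% power to detect the effect size". From Statistical Analysis: the SD of change in strength "from baseline to pretransplant is 16.8 kg". The baseline-to-follow-up correlation *r* of the secondary outcomes is not given and is an assumption, shown from 0.5 to 0.8. The true group difference of 0.8 SD is illustrative.

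**Step 1. The plan's own figure.** 1.15 × 16.8 = 19.32 kg, which matches "this study will detect a between-group mean difference of 19.3 kg with 80% power". A two-sided t test at d = 1.15 needs 13 per arm (noncentral t power 80.3%), and 13/0.9 = 14.4, rounded up to 15 per arm. The stated figure reproduces. It concerns the primary outcome only. The steps below use 13 per arm.

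**Step 2. Within-group tests when the arms do not differ.** Suppose both arms have the same true mean change δ, in units of the SD of change. Let P be the power of a two-sided paired t test with n = 13 (noncentral t, 12 df, noncentrality δ√13). The chance that exactly one arm reaches p<.05 is 2P(1−P).

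| δ | P | 2P(1−P) |
|---|---|---|
| 0 | 0.050 | 9.5% |
| 0.3 | 0.169 | 28% |
| 0.5 | 0.382 | 47% |
| 0.8 | 0.754 | 37% |

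With 14 and 13 patients the results are 9.5%, 29%, 48% and 35%. A direct between-group test gives a false-positive rate of 5% in every row.

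**Step 3. Baseline adjustment.** With equal variances at both visits, and the follow-up variance set to 1:

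- t test on follow-up values: variance 1
- t test on change scores: variance 2(1−r)
- baseline-adjusted analysis (ANCOVA): variance 1−r²

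The effective standardized difference is 0.8 divided by the square root of the variance. At r = 0.5, for example, it is 0.8/√0.75 = 0.92 for the adjusted analysis and 0.8/√1 = 0.80 for change scores. Power at 13 per arm is:

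| r | Follow-up t test | Change-score t test | Baseline-adjusted |
|---|---|---|---|
| 0.5 | 50% | 50% | 62% |
| 0.6 | 50% | 59% | 69% |
| 0.7 | 50% | 71% | 78% |
| 0.8 | 50% | 87% | 90% |

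Against change scores the variance ratio is (1−r²)/[2(1−r)] = (1+r)/2, so the saving is 25% at r = 0.5 and 10% at r = 0.8. Against follow-up values it is r², so 25% and 64%.

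**Step 4. Comorbidity index.** No arithmetic applies. The Overview lists the index only at the 30-day visit, and Statistical Analysis compares the number of comorbidities by t test. Without a value from before randomization, an imbalance that was already present cannot be separated from an effect of exercise.

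**The case against.** The strongest reply is that this is a condensed article on a 30-patient pilot, and that matching each test to each end point is commonly left to the analysis plan. That stands for the open lists taken alone: choosing only between a t test and a Wilcoxon test on follow-up values gives a simulated error of about 5% to 6%. The open menu is therefore not the basis of this point.

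A reader might infer that the plan rules out baseline adjustment. It does not. The mixed model it lists can use baseline data, and most secondary outcomes are measured three times, so that model would suit them. Adjustment is available but not specified.

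A reader might also infer that within-group p-values replace the group comparison. The documents do not say so: between-group tests are planned in the same sentence. What remains is that within-group tests are named as a means of testing a hypothesis they cannot test.

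The power gain depends on what the t test would be applied to, which the article does not state. If it is change scores, the gain at r = 0.8 is about 3 percentage points and not 40.

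Finally, the comorbidity index and length of stay are tertiary and exploratory. No baseline value is scheduled for the index, and length of stay can have none, so their unadjusted tests waste no collected data. The article gives no basis for saying that the index mainly reflects earlier comorbidity or that length of stay is skewed.

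**Conclusion.** The point holds as a readily available improvement to the secondary analysis, not as an error that undermines the trial. The article states a between-group aim, lists within-group tests under it, and names no baseline adjustment for outcomes that have baseline values, while the primary model in the same section does adjust.

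The size is as follows:

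- Reading within-group results as a group difference would mislead in 9.5% to 47% of cases over the equal-change scenarios shown. This assumes normal data, 13 per arm and the same true change in both arms.
- Baseline adjustment gives 62% to 90% power for a 0.8 SD difference, against 50% (follow-up values) or 50% to 87% (change scores). This rests on assumed correlations of 0.5 to 0.8. The adjusted analysis is better at each value shown, but the margin over change scores is small when the correlation is high.

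The primary sample size reproduces and is unaffected. The timing of the comorbidity index is a minor, separate matter for an exploratory outcome.

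**What to change.** 1. For every continuous secondary outcome, specify the baseline-adjusted mixed model already used for the primary outcome. Where there is only one follow-up, as for DEXA, specify ANCOVA with the baseline value as covariate.
2. State that conclusions on secondary outcomes rest on the between-group difference with its 95% CI.
3. Report within-group change descriptively, without p-values.
4. Minor: score the comorbidity index at baseline as well, from the medical records if they allow it, and adjust the exploratory comparison for it.

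Items 1 to 3 change wording only and use data already scheduled for collection. Item 4 adds one chart-based score per patient and no visit or procedure. The Results section reports 3 participants randomized as of October 2024, so at that stage the change could be made before any meaningful outcome data existed.

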## Results

The trial was funded in 2022 (DFCI McGraw/Patterson Research Fund from the Division of Population Sciences at the DFCI)). As of October 2024, a total of 3 participants have consented and been randomized (n=1, exercise group; n=2, waitlist control group). Trial completion and start of data analysis is expected in July 2025 with expected results to be published in early winter of 2026.

## Discussion

### Expected Findings

The primary purpose of the PROTECT Trial is to investigate if an 8-week digitally supervised prehabilitative exercise intervention improves lower limb muscle strength in patients with multiple myeloma. The PROTECT Trial provides a comprehensive assessment of physical capacity, patient-reported health outcomes, and cardiometabolic health as secondary outcomes, and evaluates patient posttransplant outcomes as tertiary outcomes. Furthermore, we will examine the effects of the patient’s self-elected exercise intervention following the ASCT recovery period to explore the benefits of prehabilitative versus rehabilitative exercise.

Outcomes from the PROTECT Trial will provide vital information on muscle strength development using a prehabilitative exercise modality in a patient population with low health status. Various exercise modalities targeting muscle strength have been assessed across cancers, with the most highly studied in breast, prostate, and colorectal cancers, and few interventions implemented within patients with multiple myeloma.

The goal of the proposed exercise intervention in the PROTECT Trial is to improve muscular strength in patients with multiple myeloma, a population more advanced in age (ie, 31.2% aged 65-74 years) [52]. The development of sarcopenia, as a result of disease-related physical inactivity due to immobility or disability (ie, fatigue in response to induction therapy, bone pain as a result of lesions due to disease progression) [53], is associated with post-ASCT complications in patients with multiple myeloma [7] and is indicated by decreased muscle strength [54]. Additionally, inflammation contributes to muscle wasting and may result from tumor cells releasing cytokines, though the biological mechanism of exercise and the inflammatory response is presently unclear in multiple myeloma [55,56]. Chronic low-grade inflammation, common in older adults (inflammaging), may also contribute to decreases in muscle mass, strength, and function (sarcopenia) through multiple pathways, primarily, mTORC1-mediated protein synthesis, metabolism, and mitochondrial biogenesis [56,57].

Proposed mechanisms for counteracting sarcopenia include reducing inflammation, promoting exercise-induced muscle hypertrophy, and decreasing fat infiltration following exercise (sarcopenic obesity) [58-60]. In fact, exercise training attenuates protein degradation signaling pathways and stimulates muscle protein synthesis, with overall anti-inflammatory and antioxidative effects that can mitigate both the sarcopenic effects and cancer-induced muscle wasting that occur [61,62]. In older adults specifically, muscle mass and function are improved with exercise, which increases the expression of insulin-like growth factor 1 and the subsequent increase of muscle protein synthesis [63]. Improved muscular function and strength following aerobic and resistance exercise interventions have been demonstrated in healthy adults and hematologic oncology populations [12,15,64]. Taking these processes and clinical populations into account, we hypothesize the proposed prehabilitative aerobic and resistance exercise intervention will target muscle protein synthesis to improve muscle strength in patients with multiple myeloma scheduled for ASCT.

Current evidence suggests muscle hypertrophy occurs with an estimated number of 18 resistance training sessions, performed over 6-10 weeks [65], which will be captured in the eight-week training period of the proposed exercise intervention. Effective resistance training oriented for hypertrophy consists of mechanical tension and metabolic stress [66] and promotes muscle protein synthesis in relation to muscle protein degradation [67]. The combination of increased muscle protein synthesis, decreased muscle protein degradation, and overall motor learning are supportive of pathways at the molecular level that lead to increased muscle mass, increased muscle force production, and overall physical strength [67]. Furthermore, resistance exercise has been implicated in stimulating the mTORC1 pathway (master growth regulator that senses and integrates diverse nutritional and environmental cues including growth factors, energy levels, cellular stress, and amino acids), which may improve mitochondrial function, increase muscle mass, and improve metabolic health, all in support of the development of muscular strength [62]. Hence, applying said principles of exercise to patients with multiple myeloma supports the primary outcome measure, improving muscular strength, of the PROTECT Trial.

Mechanisms for improvements in physical capacity, cardiometabolic health outcomes, and patient-reported outcomes along with posttransplant clinical outcomes, are described below. Exercise, particularly resistance training as noted above, stimulates muscle protein synthesis, leading to increased muscle mass and strength. However, resistance training also has the potential to improve endurance by enhancing mitochondrial function and improving motor control by neuronal growth. Cardiovascular adaptations increase oxygen transport capacity, cardiovascular health, and metabolic regulation, mitigating the risk of chronic diseases of aging. Additionally, exercise provides mental health benefits, reducing stress and enhancing cognitive function, potentially prolonging longevity and enhancing quality of life, particularly in patients with cancer undergoing pre- and posttransplant therapy.

Prehabilitative exercise, or exercise prior to medical treatment, has been successfully deployed in presurgical candidates and other tumor sites, yet there is a paucity of evidence on the effect of prehabilitation in patients receiving transplant; IMPROVE-BMT is an ongoing investigation to address this topic [68]. A recent study shows that a multimodal intervention program with partially supervised exercise training combined with nutritional support prior to transplant is feasible and safe. Patients showed improvements in fat-free muscle mass, physical performance, and health-related quality of life [69]. Additional research is needed to assess outcomes that support quality of life, overall survival, and relevant clinical outcomes along with the challenges of delivering the exercise in hospital and outpatient settings. Importantly, recent investigations indicate the acceptability and feasibility of delivering exercise prehabilitation, in person and digitally within the ASCT pathway in myeloma, but warrant further investigation on the combined effects and at the level of personalized or individualized therapy [70].

The prehabilitation intervention investigated in this study represents a novel approach to addressing the limited evidence on the benefits of prehabilitation. Prehabilitation, broadly recognized for its potential to enhance physical and psychological resilience, holds promise in optimizing outcomes for patients with cancer. Specifically, its application in the context of multiple myeloma remains understudied. The exploratory aims intend to examine the comparative effectiveness of rehabilitation versus prehabilitation, providing valuable insights into their respective contributions to patient well-being in this clinical setting.

The design of this trial includes digitally supervised, individually tailored prehabilitative exercise intervention that is progressed over the course of 8 weeks. Digital supervision allows for participants who are immunocompromised to safely complete the exercise at home and reduces the need to travel to and from the study site, outside of testing visits that are coordinated with ongoing treatment plans. Each program is designed to progress each week at 5% increments based on baseline strength and cardiorespiratory measures. The individually tailored aspect provides flexibility for patients who experience treatment-related symptoms or are able to easily manage the prescribed exercise.

### Strengths and Limitations

Strengths of this study design include a rigorously designed exercise intervention, taking into account exercise tolerance, bone pain, development of bone lesions, and limited mobility, and is individually tailored and supervised by a qualified exercise trainer. This approach supports gradual increases in load and volume over the training period and enhances program adherence. The training is conducted digitally, allowing individuals who cannot travel to the research site three times per week to participate and provides scheduling flexibility.

Limitations of this study design include a limited sample size, digital delivery, and short duration of exercise. Training is conducted remotely via a video communication platform Zoom (Zoom Video Communications, Inc), which may restrict the assessment of the full range of motion and utilization of alternative techniques to ensure the correct execution of each movement. Additionally, digital training limits the ability to assess the participant’s state through breathing and facial expressions, potentially impacting the reported RPE and the ability to monitor progression accurately.

### Conclusions

The PROTECT Trial will contribute to understanding the role of prehabilitative exercise, in a digitally supervised setting, on muscular strength outcomes in patients with multiple myeloma who receive ASCT. Findings from this trial will provide information on patient health outcomes following transplant including overall functional capacity. Understanding the limitations to exercise within this population may help develop future larger-scale exercise interventions in the prehabilitative and rehabilitative spaces that support patients with multiple myeloma from the time of diagnosis into survivorship.

## Abbreviations

ASCT: autologous stem cell transplant
DEXA: dual-energy x-ray absorptiometry
HR: heart rate
PROTECT: Prehabilitation Exercise Training in Multiple Myeloma Patients Undergoing Autologous Stem Cell Transplantation
REDCap: Research Electronic Data Capture
RM: repetition maximum
RPE: rating of perceived exertion
